PTX 400mg three times per day, was given to 9 subjects [128]. Two subjects were removed from study at weeks 2 and 5 due to initiation of prohibited concomitant drugs (inhaled steroid for bronchitis and cART for development of Kaposi Sarcoma, respectively) from their primary caregivers. FMD significantly improved after 4 weeks [median absolute increase 1.5%; p=0.04] and improved further at 8 weeks [median absolute increase from baseline 4.4%; p=0.02]. This degree of improvement in FMD has been associated with reduced risk of future cardiovascular events in the general population[21, 22]. Similar to what was observed with salsalate, 8 weeks of PTX resulted in normalization of FMD. Median NTGMD was 16% at entry and did not change over the course of the trial. It should be noted that the magnitude of improvement in FMD was similar regardless of initial FMD. . Looser stools were noticed by most of the subjects, but in none was this considered to be treatment-limiting. There were no drug-related laboratory toxicities.

We also observed in this pilot study a non-significant decline in triglycerides (p=0.09). No other lipid or metabolic parameter changed with PTX. Viral load did not change. Using an in-house HPLC assay, median plasma PTX concentrations were measured at weeks 4 and 8. The median PTX levels at weeks 4 and 8 were 73 ng/mL (270 nM) and 97 ng/mL (340 nM), respectively. There were no correlations between PTX concentrations and FMD response, which may reflect the small sample size of the study or that there is not a dose-response relationship between plasma PTX levels and FMD. We cannot rule out the possibility that intracellular levels of PTX may correlate with FMD response.

We examined the same peripheral blood markers of various potential inflammatory pathways as in the salsalate trial in order to gain insight into the pathways that may be responsible for the improvement in FMD with PTX. Because of the limited power in this pilot trial, we show in Table 1 those markers that we considered to have changed substantially, defined as either a change > 15% or a p-value < 0.05. Data are presented as median (range) due to small sample size.

Table 1. Markers of pathways that were affected by PTX.

| Biomarker* | Mechanistic Pathway | **HIV-infected Subjects Who Completed the 8 week trial of PTX (N=7)** | | |
| --- | --- | --- | --- | --- |
| Baseline  Median, pg/mL | % Change  (median) | P-value |

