As a safety measure, a peripheral IV heplock will then be placed at the IU ICRC to reduce the number of venous punctures required for the serial blood draws required to estimate insulin resistance. The heplock will also facilitate the infusion of IV fluids if NTG-induced hypotension occurs during the brachial artery reactivity testing. By performing just one venous puncture for placement of the IV heplock, the risks of bleeding, bruising, pain, and infection to the subject will be minimized; this will also reduce the risk of accidental occupational exposure of potentially infectious material to the study team. The heplock will then be removed after assurance of subject hemodynamic stability once brachial reactivity testing is completed.

Safety and adverse events will be assessed at each study visit. Study participants will be encourage to notify the study team in between these visits if symptoms occur that may be related to study drug. In the event of an adverse event possibly related to study drug, a full assessment (examination, laboratories) will be performed immediately. Study discontinuation will occur if a Grade 3 or 4 event (per Division of AIDS Toxicity Grading System <http://roc.s-3.com/members/download/adulttox.pdf>), serious adverse event, or hospitalization likely due to study drug occurs. For less severe events thought to be related to study drug, then PTX or placebo dosing will be reduced by one pill (e.g. 400mg of active agent) and symptoms, signs, and laboratories will be reassessed after one week. If the adverse event continues at the same severity or improves only modestly, then dosing will be reduced by one more pill and again the participant will be reassessed after one week. If the adverse event persists at this time, then the subject will be discontinued from the study. However, if symptoms resolve after dose reduction, then the subject will continue on study using the new dosage level. The subject, of course, will have the option of withdrawing from the study at any time. All subjects who stop study drug prematurely due to an adverse event will be followed weekly until resolution. Please see Human Subjects Protection for further details on safety monitoring.

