If subjects are excluded due to the above criteria, they may be approached again in the future or have their study visit rescheduled within the allowable timeframe if these criteria are no longer applicable. Co-enrollment into other studies will be permitted provided no drugs prohibited on this study will be given in the other study/ies and that the required blood draws do not exceed safe limits when combined with those for this study.

We are specifically excluding subjects with diabetes, hypertension, and dyslipidemia requiring therapy at screening in these two studies in order to better evaluate the role of HIV as the primary determinant of endothelial dysfunction. However, we will not discontinue study participation if these criteria develop during the course of these trials for two reasons. First, this would limit generalizability as the development of diabetes, hypertension, and severe dyslipidemia with antiretroviral therapy is common in the HIV-infected population. Second, it is possible that reduction of inflammation by PTX may theoretically prevent insulin resistance, hypertension, and hypertriglyceridemia, which are important endpoints to capture in these trials.

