6.2.2 Main Study Evaluations

There will be three main study visits where blood and urine samples will be obtained, anthropometrics performed, and brachial artery ultrasound measurements will be performed. The Week 4 visit will occur as near to Day 28 after entry as possible, but can occur as late as 42 days after entry. The Week 8 visit will occur as near to Day 56 after entry as possible, but can occur as late as 70 days after entry. Each subject will continue to take study drug/placebo until the final study visit is completed.

- - 1. Study Discontinuation Evaluations

Study subjects who complete the entry (Week 0/Day 0) procedures and have taken at least two weeks of study drug but thereafter notify the study team that they will terminate their involvement prior to the Week 4 visit will have their Week 4 evaluations performed as soon as possible after the time of notice of termination. Subjects who notify the study team that they will terminate their involvement prior to the Week 8 visit and have taken at least 6 weeks of study drug will have their study Week 8 evaluations performed as soon as possible after the time of notice of termination. Subjects who notify the study team that they will terminate their involvement within two weeks after the Week 0 or Week 4 visit evaluations have been completed will have no further evaluations performed.

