1. CRITERIA FOR STUDY DISCONTINUATION

- Request by the subject to withdraw
- Request of the primary care provider if s/he believes the study is no longer in the best interest of the subject
- If the subject is found to be pregnant or begins breastfeeding during the course of this study
- If the subject has develops fever, need for systemic therapy for acute or serious illness, or hypotension after screening that precludes completion of the main study visits within the allowed timeframes
- If the patient develops a need for antiretroviral therapy, as determined by the Principal Investigator or by the subject’s primary HIV caregiver
- Requirement for prohibited concomitant medication(s)
- Study drug-related toxicity (see section 7.0 Adverse Event Management)
- Clinical reasons believed life threatening by the physician
- Subject, as judged by the investigators, to be at risk of failing to comply with the provisions of the study protocol as to cause harm to self or interfere with the validity of the study results
- At the discretion of the funding agency

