1. STATISTICAL CONSIDERATIONS AND DATA MANAGEMENT

9.1 General Considerations

For all analyses, an intention-to-treat (ITT) approach will be used. That is, study results will be analyzed by the treatment groups to which subjects are randomly assigned, regardless of compliance in taking the medication, adherence to the protocol, and completion of the study. This trial will be a double-blind, randomized, placebo-controlled, two parallel group study. Statistical significance will be considered if two-sided p-values are less than 5%. SAS version 9.1 will be used for all statistical analyses. The software PASS was used for sample size calculation.

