9.2 Sample Size Justification

The primary endpoint is change in FMD from baseline to week 8. We used our preliminary data for estimating the detectable difference (Δ) and standard deviation for changes in FMD after 8 weeks with PTX. In the 7 subjects who completed the week 8 visit, an absolute mean (SD) improvement of 4.8% (1.34%) in the change in FMD at week 8 was observed. The 95% confidence interval was 3.5−6.0%. The correlation between week 0 FMD and week 8 FMD was 0.88. We used a very conservative approach, that is, the lower 95% confidence limit for a minimum detectable difference and assumed no change in FMD on average for the placebo group. We also used a conservative approach for estimating the standard deviation in the change in FMD. Our pilot study on 17 HIV positive patients not on cART showed a variability of 2.21 in baseline FMD. Assuming a correlation of 0.30 between week 0 and week8 FMD, we estimated the variability to be 2.62 for the change in FMD which is much higher than the variability we observed in the PTX study.

The sample size was determined based on a two-sample, independent, two-tailed t-test with 5% type I error. Samples sizes were adjusted for an estimated 20% dropout rate. A sample size of 10 per group will have at least 80% power to detect a difference in FMD of at least 3.5% assuming a common standard deviation of 2.62. To adjust for a possible 20% dropout rate, we will recruit 13 per group. The Figure below is a power curve demonstrating the ability to detect various magnitudes of treatment difference assuming a common SD of 2.62.

If a subject withdraws prior to study entry, this subject will be replaced. We expect up to 50 potential subjects will need to be screened to meet the target of 26 randomizations. If we find that the drop-out rate for those on study is greater than the anticipated 20%, then we will replace sufficient numbers of subjects so that the dropout rate is no longer greater than 20%.

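### Section 9.1 promises intention-to-treat, but leavers with under six weeks of drug have no scheduled week-8 FMD and no missing-data method is given

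*Combined protocol and SAP*

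**What the plan says.** **Target and model.** Section 9.1 applies intention-to-treat to all analyses, with subjects kept in their randomised group "regardless of compliance in taking the medication, adherence to the protocol, and completion of the study". Section 9.2 states: "The primary endpoint is change in FMD from baseline to week 8". Section 9.3.2 fits an ANCOVA to that change, with treatment, baseline FMD and selected covariates. Sections 9.1 to 9.3 name no imputation, likelihood-based or sensitivity method for a missing week-8 FMD.

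**Leaving the study.** Section 3.3 ends study participation for a Grade 3 or 4 event, serious event or hospitalisation judged likely due to drug. For milder events that outlast two dose reductions it says: "If the adverse event persists at this time, then the subject will be discontinued from the study". Section 8.0 lists drug-related toxicity, need for antiretroviral therapy and need for a prohibited medicine as reasons for study discontinuation.

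**Measurement after leaving.** Section 6.2.3 (Study Discontinuation Evaluations, directly after 6.2.2) covers subjects who tell the team they are leaving. Those who do so "within two weeks after the Week 0 or Week 4 visit evaluations have been completed will have no further evaluations performed". Those leaving before week 4 after at least two weeks of drug have the week-4 evaluations early. Those leaving before week 8 after at least six weeks of drug have the week-8 evaluations early.

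**Wording that differs.** Section 7 mostly speaks of stopping pentoxifylline, not the study, and 7.1 encourages subjects who stop drug for a Grade 1 or 2 event to complete discontinuation evaluations. The closing text of 4.2 says of new diabetes, hypertension or dyslipidemia that "we will not discontinue study participation if these criteria develop during the course of these trials", while 5.4.1 prohibits blood-pressure and lipid-lowering drugs and 8.0 removes subjects who need a prohibited drug.

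**The concern.** An intention-to-treat analysis needs the outcome from everyone randomised, whatever happened to their treatment. Here the events that interrupt treatment can also end measurement, and the primary model has no way to include a subject without a week-8 value. The comparison then rests on those who stayed, or who stayed at least six weeks.

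If staying depends on treatment or on response, the arms that remain are no longer the arms that were randomised. Sections 7.3.5 and 7.3.6 describe dose-related gastrointestinal and neurologic effects of pentoxifylline that can end in permanent discontinuation, so a treatment-linked route out exists on paper. With 13 subjects per arm, two or three such exits are a large share of the data. Scans not taken cannot be recovered at analysis.

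**Working it through.** **1. The plan's own figures reproduce.** Inputs from 9.2: baseline SD 2.21, correlation 0.30, difference 3.5, 20% dropout. The two-sided 5% level is from 9.1.
- SD of change = 2.21 × √(2 × (1 − 0.30)) = 2.615 (stated 2.62).
- Two-sample t-test, noncentral t: power 75.8% at 9 per arm and 80.6% at 10, so 10 per arm is right.
- 10 / 0.80 = 12.5, rounded up to 13 per arm.

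There is no arithmetic error. The inflation treats dropouts as supplying no primary data, so the loss is planned for. Replacing dropouts beyond 20% (9.2) restores numbers, not the randomised comparison.

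**2. Who has a week-8 FMD under 6.2.3.**

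| Notice of leaving | FMD provided |
|---|---|
| Within 2 weeks after week 0 | None after baseline |
| Before week 4, at least 2 weeks of drug | Early week 4 only |
| Within 2 weeks after the week-4 visit | Week 4 only |
| Before week 8, at least 6 weeks of drug | Week 4, and an early scan as week 8 |
| Investigator-mandated exit | Not stated |

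The third and fourth rows can collide. The week-4 visit may fall as late as day 42, which is already 42 / 7 = 6 weeks of drug, so a subject leaving a few days later meets both rules.

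The pilot shows that such timing occurs: "Two subjects were removed from study at weeks 2 and 5 due to initiation of prohibited concomitant drugs". That is 2 of 9 (22%), both under six weeks. On this timetable neither would have had a week-8 FMD.

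**3. Expected number.** At the planned rate, 26 × 0.20 = 5.2 dropouts. If exits are spread evenly over 8 weeks (an assumption), 5.2 × 6/8 = 3.9 have no week-8 FMD and 1.3 have an early one.

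**4. Possible size of the bias.** Assumptions not in the documents: a share d of the pentoxifylline arm stops early with no week-8 FMD and would keep a fraction f of the benefit at week 8; the effect in those who continue equals the design value of 3.5. Mean placebo change is 0, as in 9.2.
- All-randomised effect = 3.5 × [(1 − d) + d × f]
- Completer overstatement = 3.5 × d × (1 − f)

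| d | f | All-randomised effect | Overstatement |
|---|---|---|---|
| 20% | 1 | 3.50 | 0 |
| 20% | 0.5 | 3.15 | 0.35 |
| 20% | 0 | 2.80 | 0.70 |
| 10% | 0 | 3.15 | 0.35 |
| 30% | 0 | 2.45 | 1.05 |

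**5. Under no treatment effect.** In 100,000 simulated trials (SD 2.62, 3 of 13 missing per arm, at random on placebo, linked to poor response on pentoxifylline, t-test on observed changes), two-sided rejection was 5.7% at a latent correlation of 0.3, 7.2% at 0.5 and 16% in the extreme case of 1.0, against a nominal 5%.

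**The case against.** The strongest reply is that the loss is neither universal nor shown to be differential.

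- *A reader might infer that everyone who stops drug or starts a prohibited medicine has no week-8 FMD.* The documents do not say that. Section 6.2.3 gives an early week-8 scan after six weeks of drug, section 7 often stops or holds pentoxifylline without ending study participation, and 7.1 encourages discontinuation evaluations. The rule quoted from 6.2.3 is written for voluntary leavers. This limits the claim but does not answer it: no passage provides a week-8 scan after an investigator-mandated exit before six weeks, and the weekly follow-up in 3.3 and 7.2 does not mention FMD.
- *A reader might infer that completers are certainly not comparable between arms.* That is a risk, not a finding. The pilot reports looser stools in most subjects, treatment-limiting in none, and no drug-related laboratory toxicity. Its two losses followed an inhaled steroid for bronchitis and antiretrovirals for Kaposi sarcoma. Neither is described as drug-related, and such events could occur in either arm. Nine subjects cannot exclude intolerance.
- *A reader might take 0.7 points as the expected bias.* It is the no-retention end of an assumed range that starts at 0. Nor does the 3% figure in 2.2.1 make it decisive, because the documents cite that as an association with later events, not as a decision threshold.
- Early scans entered as week 8 may work the other way. Median pilot gains were 1.5 points at week 4 and 4.4 at week 8, so on that trend an early scan would understate the drug effect.
- Scans after antiretrovirals are hard to interpret. Section 2.2.3 reports that FMD improves on such therapy, and 2.5 and 3.1 set out to avoid that contamination. This stands, and calls for stated handling.

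**Conclusion.** The point holds in limited form. Followed as written, the plan cannot deliver the analysis that 9.1 promises. Subjects leaving with under six weeks of drug have no scheduled week-8 FMD, handling after mandated exits is unstated, and the primary ANCOVA reduces to subjects with an observed or early week-8 value.

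Whether the estimate is biased depends on why subjects leave, which the documents do not establish. With 20% early stopping in the pentoxifylline arm and a 3.5-point effect in those who continue, both assumed, the overstatement runs from 0 to 0.7 FMD points. This is a problem of estimand and missing data, not of sample-size arithmetic.

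Two document conflicts also need resolving: stopping drug against stopping the study (section 7 against 3.3 and 8.0), and 4.2 against 5.4.1 and 8.0 for subjects who develop hypertension or dyslipidemia and need drug treatment. The second is a separate inconsistency and is not needed to establish the main point.

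**What to change.** 1. **Follow-up.** In 6.2.3, 3.3 and 8.0, distinguish stopping study drug from leaving follow-up. Seek the already scheduled week-4 and week-8 FMD from every randomised subject who has not withdrawn consent, subject to the protocol's own safety and pregnancy rules. State what applies after investigator-mandated exits.
2. **Primary analysis.** Use a baseline-adjusted repeated-measures model of weeks 4 and 8. Treat baseline FMD as part of the outcome vector, so that all randomised subjects enter through baseline and any later FMD, and use small-sample degrees of freedom. Assign early scans by a pre-stated visit window, or confine them to a sensitivity analysis; do not count them automatically as week 8.
3. **Sensitivity analyses.** Add the ANCOVA on observed week-8 values, a missing-not-at-random analysis (for example, lowering the assumed week-8 change of pentoxifylline subjects without a value by 0 up to the full 3.5 points), and one setting aside FMD measured after antiretrovirals are started.
4. **Reconcile the text.** Bring section 7 into line with 3.3 and 8.0, and 4.2 with 5.4.1 and 8.0. Which clinical rule applies is for the sponsor and investigators to decide.

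The cost is protocol and consent wording plus a few retained visits, given about five expected dropouts. Off-drug data will dilute the estimate, but that diluted effect is the intention-to-treat effect the plan says it wants. The model does not rescue subjects who withdraw consent: those with only a baseline scan add little information about treatment, and the model still assumes that data are missing at random, so the third item is needed.

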6.3 Definitions for Schedule of Events – Special Instructions and Definitions of Evaluations

6.3.1 Documentation of HIV-1 Infection

HIV-1 infection, as documented by any licensed ELISA test kit and confirmed by Western blot, must be present in the source documentation at the first screening visit. HIV-1 culture, HIV-1 antigen, plasma HIV-1 RNA, or a second antibody test by a method other than ELISA is acceptable as an alternative confirmatory test.

- - 1. Medical History

A medical history must be present in the source documents. Record the following on CRFs:

- Birthdate
- Sex
- Patient’s self report of ethnicity and race
- Initial date of HIV infection documentation
- Route of HIV infection
- Baseline, nadir, and most recent CD4 cell count (including dates of these values)
- Baseline, peak, and most recent HIV-1 RNA level (including dates of these values)
- Family history of cardiovascular disease
- Smoking history
- Menstrual cycle history (date of onset of last menstrual period)

- - 1. Medication History

A medication history must be present in source documents. The following information will be recorded on the CRFs:

- Complete HIV treatment history, including start and stop dates of any antiretroviral medication (estimated if the exact dates cannot be obtained), immune-based therapy, or HIV-related vaccines, including blinded study medications
- Aspirin or other NSAID use within 28 days prior to study entry
- Immune-modulating drugs within 28 days prior to study entry
- Any other prescription medications, within 28 days prior to entry
- Any vaccinations, within 28 days prior to entry
  - 1. Concomitant Medications

All new and/or discontinued prescription medications taken since the last clinic visit will be recorded on CRFs with start and stop dates. It is critical to have complete information on off-protocol use of aspirin or other NSAIDS. It is also critical to document the date(s) of receipt of any vaccinations since the last clinic visit.

- - 1. Pentoxifylline Dosing Modifications

All modifications to pentoxifylline dosing including initial doses, subject-initiated and/or protocol-mandated interruptions, modifications, and permanent discontinuation of treatment will be recorded on the CRFs at each visit. Subject-initiated and protocol-mandated interruptions include both inadvertent and deliberate interruptions of pentoxifylline doses for > 4 days.

- - 1. Family History

A family history of cardiovascular disease must be present in the source documentation and recorded on CRFs at entry.

- - 1. Smoking History

The subject’s past and current tobacco use must be present in the source documentation and recorded on CRFs at entry.

- - 1. Clinical Assessments

